**Primary objectives**
To assess the feasibility of using data from patients’ own wearable sensors for assessments in acute care. Feasibility will be assessed by eligibility, recruitment, retention rates, and patients’ acceptability.

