**Main study end point**
To quantify the proportion of patients assessed for an acute complaint who are wearing a device that collects data on vital signs (ie, heart rate and step count).

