### Study Procedures

All patients aged 18 years and older who present to acute care will be asked if they wear a smartwatch, activity tracker, or wearable that measures heart rate.

Patients will be asked to give informed consent in line with the guidance from the participating countries. This is likely to include written informed consent in the Netherlands, Denmark, and the United Kingdom. Informed consent will be explicit about accessing data from patient-held wearables (Multimedia Appendix 1). Once consent has been obtained, initial data will be entered into the case report form, and the remaining items of the case report form will be completed on the day after the initial presentation or later (Textbox 3). Study documentation will include a guide for investigators to interrogate commonly used wearable devices (Multimedia Appendix 2). Parameters recorded will vary according to the different devices used but should at least include heart rate and step count.

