Data items were collected as part of the "Feasibility of Using resting heart rate and step counts from patient-held Sensors during clinical assessment of medical Emergencies" (FUSE) study.Site ID is the unique number for each site.Participant ID is a consecutive number (no identifiable information is collected).Location is the location where the patient is included in the study (ie, emergency department, medical admissions unit, ambulatory emergency care, or other).Sex as reported by the patient (ie, men, women nonbinary, or unknown).Date of birth, which will be used to compute an age category.Date and time of first presentation, defined as the time that a patient presents at the location.Highest level of education is the patient finished highest level of education or the level of education the patient is currently following (ie, primary school, secondary school, and higher education).Digital literacy is assessed using 2 questions asking for confidence of using the internet and confidence of using mobile apps, which patients can answer using a 5-point Likert scale.Device is the device used to measure heart rate, and the brand and type will be recorded.Phone is the phone that patients use, and this will be used to retrieve the step count and heart rate data. The brand and type will be recorded.Heart rate on the device is the heart rate that is stored and measured by the device, and the resting heart rate (as presented by the device), the minimum, maximum, and mean or median (depending on the device) will be retrieved on three-time points, namely on presentation, within 24 hours before presentation and within 1 week (plus or minus 1 day) before presentation.Walking distance is the number of steps of exact distance (in kilometers or miles), either measured by the device of the phone. The daily walking distance of the 7 days before the presentation will be recorded.Frailty as quantified through the Clinical Frailty Scale [19].Mobility will be assessed as either normal or impaired. Mobility is considered impaired if the patient is unable to get onto the bed unaided, either from the ambulance gurney or whichever way they arrive.Date and time of the first set of vital signs is defined as the time that the first set of vital signs are measured.Heart rate on admission is the first heart rate measured during clinical examination.National Early Warning Score [9] as a standardized assessment of the severity of illness, based on the first full measurements of respiratory rate (per minute), oxygen saturation (in %), temperature (in °C), heart rate (per minute), systolic blood pressure (in mm Hg), AVPU (alert, verbal, pain, and unresponsive) score, and the use of any supplemental oxygen.Outcome is assessed at midday on the day after the initial assessment and can be (ie, discharged, admitted to hospital, admitted to high care or intensive care, or deceased).

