#### Primary Outcome Measures

The primary outcome of the study will be feasibility as assessed by the proportion of eligible patients with emergency presentations who have devices as well as recruitment and retention rates.

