## Results

Approvals have been completed in 11 sites in Denmark, 17 sites in the Netherlands, 1 site in Switzerland, and 7 sites in the United Kingdom.

The main FUSE study has gone live on the May 15, 2024, in 34 hospitals in the Netherlands (n=17), the United Kingdom (n=7), Denmark (n=9), and Switzerland (n=1). A total of 1137 patients were screened, of these, 452 patients were included and 209 patients had data on at least 2 collection points, allowing for an analysis of trends.

Preliminary analysis will be completed by December 31, 2024, and the main manuscript will be submitted for publication by the end of March 2025.

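### The main end point counts device wearers among all patients assessed, but the article provides for recording device data only after consent, so device use and recruitment cannot be separated

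*Protocol article*

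**What the plan says.** - **Main study end point (Textbox 2):** "To quantify the proportion of patients assessed for an acute complaint who are wearing a device that collects data on vital signs". The denominator is patients assessed, and joining the study is not part of the definition.
- **Primary Outcome Measures:** feasibility is judged by "the proportion of eligible patients with emergency presentations who have devices as well as recruitment and retention rates". The denominator here is eligible patients.
- **Primary objectives (Textbox 1):** "Feasibility will be assessed by eligibility, recruitment, retention rates, and patients’ acceptability".
- **Inclusion criteria:** using a wearable is a condition of entry. A smartphone that collects step counts also qualifies.
- **Study Procedures:** "All patients aged 18 years and older who present to acute care will be asked if they wear a smartwatch", and then "Once consent has been obtained, initial data will be entered into the case report form". Recruitment and Consent gives the same order: device question, information, consent.
- **Data items (Textbox 3):** "Device is the device used to measure heart rate, and the brand and type will be recorded". The phone is a separate item. No item holds the answer to the screening question, eligibility, refusal or a reason for non-inclusion.
- **Governance:** units are asked to gather data on everyone presenting in the study areas over 24 hours. What is kept for those who do not consent is not stated.
- **Results:** "A total of 1137 patients were screened, of these, 452 patients were included".

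**The concern.** The proportion of patients who wear a device is a fact about everyone asked. A wearer who declines still belongs in the numerator. The recruitment rate is a different quantity: of the eligible device users, how many joined. Both are named as primary feasibility measures, and both need the number of device users found at screening. The article asks the question that would yield this number. Yet it describes data entry only for those who consent, and lists no item in which the number would be held.

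The denominators add to the difficulty. Since device use is an inclusion criterion, the proportion of eligible patients who have devices is 100% by construction if read literally. Recruitment and Consent calls patients eligible before they are asked about a device, so the word carries two meanings.

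At stake is the headline result. If included over screened is taken as device use, it carries an error that depends on consent and on phone-only inclusion, and more patients would not shrink that error.

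**Working it through.** **Planned size.** Sample Size Calculation assumes 40 hospitals screening up to 50 patients each: 40 × 50 = 2000, which reproduces the stated figure (strictly a maximum, given the words up to). The study is thus sized on patients screened, which fits the main end point but not consent-first entry.

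**Inputs.** From Results: S = 1137 screened, I = 452 included. Not in the documents, so assumed: c, the share of device users who enrol (0.7 to 1.0 here), and w, the share of the included who wear a device rather than only carrying a phone (0.6 to 1.0 here).

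**What the counts give.** I/S = 452/1137 = 39.8% (Wilson 95% CI 36.9% to 42.6%). The other 1137 − 452 = 685 are not split into no device, declined, unable to consent or too ill.

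**Why the two rates cannot be separated.** Let D be the number of screened patients with a qualifying device.

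- Device use = D/S.
- Recruitment among device users = I/D.
- Their product is I/S = 39.8%, whatever D is.

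D can lie anywhere from 452 to 1137. Device use could therefore be 39.8% to 100%, with recruitment running from 100% down to 39.8%.

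**Size and direction.** With D = I/c, use of any qualifying device is I/(cS). If wearable and phone-only users enrol at the same rate (a further assumption), the share wearing a device is wI/(cS) = (w/c) × 39.8%:

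| | c = 1.0 | c = 0.9 | c = 0.8 | c = 0.7 |
|---|---|---|---|---|
| w = 1.0 | 39.8% | 44.2% | 49.7% | 56.8% |
| w = 0.8 | 31.8% | 35.3% | 39.8% | 45.4% |
| w = 0.6 | 23.9% | 26.5% | 29.8% | 34.1% |

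For wearing a device, 39.8% is too low when w exceeds c, too high when w is below c, and right only when they happen to be equal.

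**Against sampling error.** The half-width at n = 1137 is 1.96 × √(0.3975 × 0.6025/1137) = 2.8 points. With w = 1, the understatement 39.8% × (1/c − 1) passes 2.8 points once c falls below about 0.93. At c = 0.9 it is 44.2 − 39.8 = 4.4 points.

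**The case against.** The strongest reply is that this rests on the silence of a condensed article. Nothing in the itemised list could produce a count of screened patients, yet 1137 is reported, so records were kept outside that list. Governance asks for data on everyone presenting, and a screening log is commonly left to the full protocol or site documents. Results is a brief status report, and a breakdown missing there may still have been recorded. All of this stands. A reader might infer that device users who declined were in fact lost from the numerator, but no section says so.

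Three further readings go too far:

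- *That the plan will report 39.8% as device use.* No section says this, and Primary Outcome Measures names the device proportion separately from recruitment.
- *That device use and recruitment become one and the same number, with 39.8% a floor for the main end point.* A phone alone qualifies for inclusion, so some of the 452 may wear nothing. The Device and Phone items could separate these groups among the included.
- *That differences in device use between age groups would be distorted.* The article plans to describe device users and compare them with national surveys. It does not plan prevalence by age group among those screened.

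Patients unable to consent are also a declared exclusion, not a data-capture failure. What is open for them is whether they count among patients assessed.

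The reply does not remove the core point. A count of patients screened is not a record of their device answers. The article itemises its data and states when entry begins, and at that level of detail its sections on the main end point do not agree.

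**Conclusion.** The point holds as a failure to fix how the main end point is captured and over which denominator; it does not show that data were lost. As described, device use and recruitment cannot be told apart, and the reported counts give only included over screened, 39.8%. That could understate device use (by 4.4 points at an assumed 90% enrolment and 9.9 points at 80%, if all included wear a device). It could also overstate the share wearing a device (true value 31.8% if an assumed 80% of the included are wearers and every device user enrols). The enrolment rates and wearer shares are assumptions; the documents give neither. The point would fall away if the full protocol or site logs recorded the device answer of every patient asked and the denominators were stated. The change should be made, because it concerns the main end point and costs little.

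**What to change.** 1. Reconcile Main study end point, Study Procedures, the data items, Primary Outcome Measures and Governance. State one denominator for device use, say whether patients who cannot consent or are too ill count in it, and do not use the word eligible for patients not yet asked about a device.
2. Keep an anonymous one-line tally for every patient asked: device category (none, phone only, wearable) and what followed (included, declined, unable to consent, too ill). Add age group if prevalence by group is to be reported; without it, the tally cannot correct for consent that differs by age.
3. Compute device use as wearable users over all asked, whether or not they consented. Compute recruitment as included over eligible device users.
4. For data already collected, take these counts from site screening logs. Where a site has none, report included over screened under that name, neither as the main end point nor as a lower bound for it.

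The cost is one line per patient without identifiers, a sentence each in Study Procedures and the data list, and possibly a note to the ethics committees. Since the main study week is over, the tally itself can serve only later rounds. For the present data, the work is retrieving logs and labelling the result correctly.

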## Methods

### Study Design

A pilot study was performed at a single site in the United Kingdom to develop and test procedures for data collection and reporting during the previous 6 months. Based on the learning from this pilot a prospective, international, multicenter, observational study using the flashmob research design will be conducted [18]. Participating units will collect data from patients presenting with acute medical emergencies to emergency departments, acute medical units, and ambulatory emergency care. There will be no randomization, blinding, and treatment allocation.

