**Secondary study end points**
Secondary end points will focus on four areas of interest:The difference between the heart rate at rest from the wearable device 24 hours, 1 week, and 1 month before assessment by emergency practitioners compared with the first set of vital sign parameters measured on admission to acute care.The change in daily steps taken in the month before admission to acute care.To describe the population that is wearing devices that collect data on vital signs in terms of gender, age group, severity of illness as measured by a standard set of vital signs, level of education, and digital literacy and frailty.To explore the association of changes in heart rate from the community to assessment in acute care services with clinical end points such as admission to a general ward or admission to a critical care area or discharge home within 24 hours from the time of clinical assessment.

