#### Secondary Outcome Measures

Secondary outcomes measures include measures of epidemiology and physiology:

We will report trends for heart rate and step count, specifically the difference between the heart rate at home 24 hours, 1 week, and 1 month before clinical assessment from the wearable device compared with the first vital signs measured on admission to acute care as both an absolute and a proportional change.

We will also describe the degree of association between changes to vital signs from the community to assessment in acute care services with admission to a general ward or admission to a critical care area or discharge home within 24 hours from the time of the first hospital assessment.

The population wearing or carrying devices will be described in terms of gender, age, ethnicity, level of education, and digital literacy and contrasted with data from national surveys.

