## Discussion

### Anticipated Findings

While sensors that can be carried or worn are in widespread use with a project market size in 2023 of in excess of US $4 billion [20], previous research has found little evidence of their use in emergency care [21]. This study aims to determine if there are opportunities to use the data generated by these consumer-held devices to improve patient care. Trends in vital signs and mobility are used to quantify risks to patients and are likely to become more important as the proportion of patients with chronic conditions (and abnormal vital signs during signs of clinical stability) is increasing. For clinical use we anticipate a number of use cases: Assessing patients whose vital signs have not changed in the week previous presentation in an acute care setting might reassure clinicians that the condition is overall stable and that treatment in the community is likely to be safe. Assessing patients whose vital signs have significantly changed in the days or hours before presentation might increase the confidence of clinicians to admit for observation and treatment in the hospital. This type of decision-making is commonly undertaken during an initial observation phase in emergency departments or acute medical unit with patients being observed for a night before committing to a decision about admission or discharge. We anticipate that this type of decision-making could be undertaken during the initial presentation if data on markers of physiological instability is available already at this point.

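### Presentation is timed from arrival at the enrolling unit, so for patients enrolled after transfer the 24-hour heart rate and the last daily step count can include hospital time

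*Protocol article*

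**What the plan says.** The data items in Study Procedures (Textbox 3) first fix the place: "Location is the location where the patient is included in the study". The emergency department and the medical admissions unit are separate options. They then fix the time: "Date and time of first presentation, defined as the time that a patient presents at the location".

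The device data are counted back from that time. Heart rate is retrieved at three points, "namely on presentation, within 24 hours before presentation and within 1 week (plus or minus 1 day) before presentation". For steps, "The daily walking distance of the 7 days before the presentation will be recorded".

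Two other sections use different anchors. The secondary end points (Textbox 2) compare the admission values with resting heart rate "24 hours, 1 week, and 1 month before assessment by emergency practitioners". Secondary Outcome Measures reports "the difference between the heart rate at home 24 hours, 1 week, and 1 month before clinical assessment from the wearable device", which makes clear that these are meant to be home values.

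Study Design has sites enrol in "emergency departments, acute medical units, and ambulatory emergency care". The article neither excludes patients who pass from one of these areas to another nor says how their times are to be coded.

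**The concern.** The study uses the patient as his or her own reference, so the earlier device value must come from before the hospital episode. For a patient enrolled where he or she first arrives, arrival at the unit and arrival at the hospital coincide, and nothing goes wrong. For a patient who reaches the emergency department, stays some hours and is enrolled in the admissions unit, the stated definition puts time zero at the second arrival. Hours of rest, monitoring and treatment in hospital then sit inside the period labelled as home.

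The clinical comparator is also affected. It is the first heart rate taken at clinical examination and is not tied to the enrolling unit. If it was taken in the emergency department, it falls before the coded presentation, inside the window against which it is compared.

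At stake are the shortest-term heart rate change, the last point of the step trend, and their relation to disposition.

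**Working it through.** No figure in the article rests on this point, so there is none to reproduce. The check is of definitions, followed by an illustration.

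**Anchors side by side**

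| Section | Counts back from |
|---|---|
| Study Procedures, data items | arrival at the enrolling location |
| Secondary study end points | assessment by emergency practitioners |
| Secondary Outcome Measures | clinical assessment |

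These broadly agree for a patient enrolled at the first point of arrival. For a patient enrolled downstream, the first can be hours later than the other two.

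**Share of each window that is hospital time**

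Let h be the hours in hospital before arrival at the enrolling unit. The documents give no value; 2 to 12 hours is an assumption.

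- 24-hour window, share h/24: 2/24 = 8%, 4/24 = 17%, 6/24 = 25%, 8/24 = 33%, 12/24 = 50%.
- 7-day step window (7 × 24 = 168 hours), share h/168: 2/168 = 1.2%, 12/168 = 7.1%. All of it lies at the end of the window. A stay of up to 12 hours crosses at most one midnight, so at most one calendar day before the day of presentation is touched.
- 1-week heart rate, read as a time point 7 days ± 1 day back, that is 144 to 192 hours: overlap is max(0, h − 144), which is 0 for any stay up to 144 hours.
- 1-month heart rate: further back still, so no practical overlap.

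**What a clock-time share does to a mean**

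Let f = h/24, B the mean heart rate at home, H the mean in the hospital hours, and A the first clinical heart rate.

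- Window mean = (1 − f)B + fH.
- Reported change = A − window mean = (A − B) − f(H − B).
- If H = A, the change shrinks to (1 − f)(A − B): 92% of its true size at h = 2, 50% at h = 12.
- If H is below B, for instance after rest and treatment, the change is overstated.

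So even for a mean the direction is not fixed. The formula does not apply to the minimum, the maximum, a median or the device's own resting value. Hospital hours can set a new minimum or maximum, but not in proportion to f.

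**With presentation at first hospital arrival**

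The share of hospital time from the same episode is 0 in every window, whatever h is.

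**The case against.** The strongest reply is that the damaging reading is not the only one. The item is labelled as first presentation. The mobility item speaks of how the patient arrives, which suits enrolment at the front door. Both end point sections point to the first assessment, which for a transferred patient would usually be in the emergency department. This has force: many sites may have coded hospital arrival. But the definition itself names the location, and the location is defined as the place of inclusion. At best, two sites could date the same patient differently.

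Three stronger readings are tempting, and the documents do not support them.

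- A reader might infer that every device window is compromised. The arithmetic shows otherwise: only the 24-hour heart rate and the last step day are exposed.
- A reader might infer a large spurious gap between admitted and discharged patients, since transferred patients are plausibly mostly those being admitted. The documents give neither the share transferred nor their hospital hours. They also do not suggest that discharged patients are spared: Anticipated Findings describes decisions "undertaken during an initial observation phase in emergency departments or acute medical unit with patients being observed for a night" before either admission or discharge is settled. Neither the size nor the direction of a difference by disposition can be derived.
- A reader might infer that transferred patients were screened twice and distort the device-use denominator. No one-entry rule is stated, but an article commonly leaves such screening rules to the full protocol, and nothing indicates that it happened.

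It is also fair to say that the primary outcome (device use, recruitment and retention) does not depend on these windows.

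**Conclusion.** The point holds in a limited form. A stated definition, not a missing detail, misdates patients enrolled after transfer and disagrees with the anchors in the two end point sections. For these patients the 24-hour heart rate summaries can contain hospital hours, the last daily step count can do so if the stay crosses midnight, and the first clinical heart rate can precede coded presentation. Under the assumed 2 to 12 hours of prior stay, 8% to 50% of the 24-hour window is hospital time. That is a share of the clock, not a bias in beats per minute.

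The number of such patients is unknown. Results reports 209 patients with data on at least two collection points, so a modest number of misdated records could matter to the short-term trend, but the documents do not show that there were any. The effect is confined to secondary analyses.

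**What to change.** 1. Define presentation as first arrival at the hospital for the episode, whichever area enrols the patient. Record arrival at the enrolling unit separately if it is wanted.
2. Count the device windows and step days back from that time, and use the same anchor in Study Procedures, the secondary end points and Secondary Outcome Measures.
3. Data collection is complete, so use what was recorded. The time of the first vital signs is a separate item: flag every record in which it precedes the coded presentation. Re-anchor those records where the site can still retrieve the arrival time; otherwise exclude their 24-hour and last-day values in a sensitivity analysis.
4. The flag misses a transferred patient whose first vital signs were entered from the enrolling unit, so also show the 24-hour and last-day results by Location.

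The cost is one reworded definition and a look-up of arrival time in the hospital record. For data already collected, the look-up depends on sites being able to link the anonymous study number to the record. Where they cannot, the sensitivity analysis needs no new data.

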#### Data Analysis

Data will be analyzed using SPSS (version 28; IBM Statistics). All variables will be assessed for normality. This study will use basic epidemiological data to determine if patient-owned monitoring devices can be used in an emergency care setting to assess the patient’s current severity of illness and compare it with their usual state of health.

Continuous data will be analyzed using the unpaired *t* test (if the data are normally distributed) or the Wilcoxon rank sum test (if the data are not normally distributed). Changes between measurements will be described as percentage change from the first measurement taken at home before admission as the assumed baseline and as an absolute change. Categorical data will be analyzed using chi-square test. Basic statistics and descriptives will be used to identify the distribution of patient and device characteristics. Missing data will not be imputed.

Associations between the baseline measurements and the specified clinical end points and the absolute and proportional change of physiological measurements and the specified clinical end points will be assessed using linear regression and logistic regression.

Patient characteristics will be expressed as absolute numbers per (sub)category for the total patient population, the discharged patients, and the admitted patients. The heart rate and step count data will be compared for their respective average or median for the different time points. Both will be tested for significant interaction between time, disposition, and change in either heart rate or step count using a generalized linear model.

For secondary exploratory analyses, the correlation between potential outcomes will be tested using Pearson coefficient correlation analysis (*r*), where the following interpretation will be used: below 0.10 negligible, between 0.10 and 0.39 weakly correlated, between 0.40 and 0.69 moderately correlated, between 0.70 and 0.89 strongly correlated, and above 0.89 very strongly correlated. The percentile change in heart rate and step count will be calculated in comparison to the baseline, which will be assumed to be at 30 days before a hospital visit.

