#### Governance

Hospitals will be recruited across Europe and coordinated by the study steering board. The study steering board consists of the principal investigators and members of the Safer home consortium. Centers are encouraged to collect data on a small cohort of patients before the main study week (May 10-22, 2024). During the main study week, all participating units are asked to collect data on all patients presenting in the study areas during a 24-hour period.

Participating countries will be responsible for their own submission for approval and coordination of research.

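### Within a unit that enrols in one 24-hour period, seven daily step values cannot separate change over time from the ordinary weekday pattern, nor can they supply the month or 30-day baseline named elsewhere

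*Protocol article*

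**What the plan says.** The step data are fixed in the data items under Study Procedures: "The daily walking distance of the 7 days before the presentation will be recorded". The same list records the date and time of first presentation.

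Governance fixes enrolment for the main study: "all participating units are asked to collect data on all patients presenting in the study areas during a 24-hour period". The period falls in a main study week dated May 10-22, 2024. Governance also allows some earlier enrolment: "Centers are encouraged to collect data on a small cohort of patients". Results gives a start date: "The main FUSE study has gone live on the May 15, 2024, in 34 hospitals".

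The secondary end point for steps covers a longer span: "The change in daily steps taken in the month before admission to acute care". Data Analysis names two baselines. One is "percentage change from the first measurement taken at home before admission as the assumed baseline"; the other is a baseline "which will be assumed to be at 30 days before a hospital visit". Data Analysis also compares heart rate and steps across time points and tests an interaction involving time and disposition in a generalized linear model. No section mentions weekday, weekend or a matched reference week. Limitations assumes only that each person's pattern of device use is constant over time.

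**The concern.** The step objective is a within-person contrast over time: steps shortly before presentation against steps when well. Seven consecutive days contain each weekday exactly once, so no two recorded days can be compared on the same weekday. If all patients in a unit present on one date, day -1 is the same weekday for all of them, and so are days -2 to -7. A weekday-weekend difference in walking then takes the same shape as a change before illness. Patients in that unit share the error, so more patients on the same date do not reduce it.

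The main effect of time on steps is at stake, which is one secondary end point. The Discussion expects clinicians to draw on changes in the days before presentation, so a false trend would matter for how the result is used. A second week of steps is a data-collection choice that no analysis plan can supply later.

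**Working it through.** **Planning figure.** The protocol gives no numerical assumption for steps. Its only planning figure, 40 hospitals × 50 patients = 2000 screened, reproduces and has no bearing on this point.

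**Inputs from the protocol.** Daily steps on days -7 to -1; one 24-hour period per unit; a window of 22 - 10 + 1 = 13 calendar days; go-live on May 15, 2024, a Wednesday by the calendar; baselines as stated above.

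**Input assumed.** Weekend steps lower than weekday steps by e = 20% (range 10% to 30%), with no true change. The protocol gives no such figure.

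**Step 1: can the effects be separated?** Take a model with an intercept, six indicators for day before presentation and one weekend indicator (8 columns).
- One enrolment weekday: rank 7 of 8, so the weekend effect cannot be separated from time.
- Two adjacent enrolment weekdays: rank 8 of 8.
- All seven weekdays: rank 8 of 8.

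**Step 2: false fitted change.** The days have mean -4 and sum of squares 9+4+1+0+1+4+9 = 28. With weekday level 1 and weekend level 1 - e, the least-squares slope is -e × S / 28, where S is the sum of (day + 4) over the two weekend days. The fitted change from day -7 to day -1 is 6 × slope, as a share of the weekday level. For Monday, S = 2 + 3 = 5, and 6 × (-0.2 × 5 / 28) = -21.4%.

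**Step 3: single-day contrasts.** These are ratios of the two days' levels: 0.8/1 - 1 = -20%, or 1/0.8 - 1 = +25%, or 0 when both days are of the same type.

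Results at e = 20%:

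| Presentation day | Weekend falls on | S | Fitted change, day -7 to -1 | Day -1 vs day -7 | Day -1 vs day -30 |
|---|---|---|---|---|---|
| Mon | -2, -1 | 5 | -21.4% | -20% | 0 |
| Tue | -3, -2 | 3 | -12.9% | 0 | +25% |
| Wed | -4, -3 | 1 | -4.3% | 0 | 0 |
| Thu | -5, -4 | -1 | +4.3% | 0 | 0 |
| Fri | -6, -5 | -3 | +12.9% | 0 | 0 |
| Sat | -7, -6 | -5 | +21.4% | +25% | 0 |
| Sun | -7, -1 | 0 | 0 | 0 | -20% |

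Over e = 10% to 30%, the fitted change is -10.7% to -32.1% for Monday and -2.1% to -6.4% for Wednesday. Averaged evenly over the seven presentation weekdays, it is 0.

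**Step 4: the 30-day baseline.** Thirty days is not a multiple of 7, and neither is the 29-day gap from day -30 to day -1, so this baseline does not match weekdays. Days -7 to -1 do not contain day -30 in any case.

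**Step 5: time by disposition.** Fitting day, disposition and their interaction with a weekend effect common to both groups gives interaction terms of 0. Only the main effect of time carries the pattern.

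**The case against.** Several objections have force.

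- **The alias need not survive pooling.** Units may have used different dates in the 13-day window, an earlier small cohort is encouraged, and a 24-hour period that crosses midnight covers two weekdays. Any of these can restore full rank if weekday is modelled. A reader might infer from the May 15 go-live that all units enrolled that Wednesday. The protocol does not say so, and it gives no dates by unit.
- **The size depends on the summary chosen.** If all units had enrolled on a Wednesday, day -1 against day -7 would be unbiased and the fitted trend small. A reader might also compute day -1 against the mean of the six earlier days and get other figures, but the protocol defines no such contrast.
- **The planned contrast by disposition is protected** when both groups share the weekday pattern.
- **Weekday can already be derived** from the recorded presentation date, and a weekday term is a model detail that an analysis plan could hold.

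All of this stands and narrows the point. It does not answer the within-unit problem: with seven days and one date, no later analysis can supply a same-weekday comparison. Nor does it remove the conflict between seven recorded days and the month or 30 days named elsewhere, which is the firmer part.

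**Conclusion.** The point holds in limited form. In a unit enrolling on one date, and in the pooled data if most units share a weekday, the main effect of time on steps cannot be separated from a weekday-weekend pattern. Under the assumed 20% weekend reduction, the false fitted change runs from about -21% (Monday) to +21% (Saturday), with about -4% for Wednesday and 0 for Sunday. Day -1 against day -7 is biased only for Monday (-20%) and Saturday (+25%). The sign and size depend on presentation weekday, on the summary and on the assumed effect.

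A reader might go further and infer that the study will report a weekend effect as illness, or that the bias can never be removed. The documents support neither: they give no weekend effect and no enrolment dates by unit, and varied dates would let a pooled model separate the two. Separately, and without any assumption, the seven recorded days cannot supply the month in the end point or the 30-day baseline.

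**What to change.** 1. **Reconcile the data item with the end point and baseline.** Record daily steps for at least days -14 to -1. Days -28 to -1 or longer are preferable, because 14 days match weekdays but do not cover the stated month. Replace the two baselines with one that the recorded days can supply.
2. **Define step change on matched weekdays:** the last 7 days against an earlier 7-day block, or day -1 against day -8 (or day -29, if that day is recorded).
3. **Derive weekday from the recorded presentation date** and include it in the pooled step model. No separate date for each step value is needed.
4. **Where only seven days exist,** report the step trend by presentation weekday and limit conclusions to the admitted-versus-discharged contrast.

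The Abstract reports that the flashmob study has concluded. For those data, items 3 and 4 remain feasible; items 1 and 2 serve any further data collection and the later studies foreseen in the Conclusions. The cost is some additional daily values per patient, read from the same device (7 more for two weeks, 21 more for four), plus the weekday adjustment in the model.
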